### Statistical considerations

#### Sample size

The sample size of 150 patients is based on a realistic recruitment target and according to a Bayesian decision rule for the primary outcome. Our decision rule would be that progression to an international definitive trial is indicated if the observed posterior probability of a positive treatment effect is 80% or greater. A simulation-based approach was used to estimate posterior probability of a positive difference in time in euglycaemia (in favour of the Freestyle Libre). The following assumptions were made, based on previous published data,^22^ as well as unpublished data from 14 patients each providing measurements of time in euglycaemia for 7 days:

mean time per day in euglycaemia of 13.3 h in the control group;mean time per day in euglycaemia of 14.8 h in the intervention group (effect of 1.5 h);between-patient variance of 32.90;residual (within-patient) variance of 10.97;intra-class correlation of 0.75;minimum of 9 days complete data per patient, with days 10-14 each having an independent 20% chance of being unobserved.

Based on 1000 simulations, the expected posterior probability of the difference in the time in euglycaemia (defined in study participants as glucose levels between 3.9-10.0 mmol/l) between the groups being greater than zero (conditional on 1.5 h being both the observed and true difference) would be 0.958 (90% interval 0.946–0.97). In the same scenario, if 20% of participants are lost to follow-up, then the expected posterior probability would be 0.939 (0.921, 0.957). The posterior probabilities calculated assumed an uninformative prior distribution. Table 2 summarises the expected standard errors from the simulations, and the mean (90% percentile interval) of the posterior probabilities for a range of sample sizes and potential observed intervention effects. In summary, with 150 patients, there is a high chance (>90%) of concluding a treatment benefit if the true difference between the groups is at least 1.5 h.

**Table 2. table2-1479164120957934:** Results of simulations to estimate standard errors from primary analysis models and expected posterior probabilities of concluding a positive treatment effect. Mean probabilities are given with 90% intervals for the posterior probabilities observed in the simulations. *d*^= observed (and true) treatment effect.

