The primary outcome measure will be analysed and interpreted within the Bayesian framework, estimating and reporting the posterior probability of a positive effect. If this posterior probability is 0.8 or more, then this would indicate that moving to a definitive trial is recommended. The primary analysis will use proper but uninformative prior distributions for all parameters in the model. Sensitivity analysis will consider more informative priors, based on previous published data, as sensitivity analyses.^27,28^ The outcome measure itself will be the time in each individual 24-h period that the patient’s glucose spends in the range [3.9, 10.0 mmol/L], thus each patient will have multiple readings within the 76 to 91 day range. These will be analysed using a hierarchical longitudinal repeated measures model, comprising random intercepts for patients and centres, and random slopes for time, as well as fixed effects for intervention arm, insulin use, time, time-by- intervention interaction and day 0 time in range. We will initially assume a linear effect of time, but alternative patterns of change will be considered when data are available. The Bayesian posterior probability of positive intervention effect will be reported, when using prior distributions for main effects and covariances that are proper and non-informative. An additional analysis will account for possible moderating effect of baseline insulin use on the outcome measure, by including a fixed effect for the interaction between baseline insulin use and the intervention arm. Finally, for an ancillary analysis, we will obtain a single mean average time per day in normal range for each patient, and fit a conventional linear regression model, adjusting for fixed effects of insulin use, mean baseline glucose level and random intercept effects for randomising centre. This analysis will allow comparison between our results and other published trials using such analysis approaches.

Table 3 lists the planned analysis approach for the secondary and exploratory outcome measures. In general, analyses will take the form of regression models that adjust for the stratification factors, reported as estimated effect sizes with 95% confidence intervals. Analyses of “time per day” with glucose in a given range will be derived and analysed analogously to the primary outcome measure, though not within the Bayesian framework.

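### The >90% chance of concluding benefit at a true 1.5 h is a posterior probability at a fixed estimate; the stated 0.80 rule is met about 81% of the time (about 76% with 20% loss)

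*Protocol article*

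**What the plan says.** The Sample size section gives one decision rule: "progression to an international definitive trial is indicated if the observed posterior probability of a positive treatment effect is 80% or greater". The Analysis methods section repeats it: "If this posterior probability is 0.8 or more, then this would indicate that moving to a definitive trial is recommended". No other criterion for the primary outcome is stated.

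For 150 patients and an effect of 1.5 h, the section reports an expected posterior probability of 0.958 (90% interval 0.946 to 0.97), and 0.939 if 20% of participants are lost. It gives the condition openly: "conditional on 1.5 h being both the observed and true difference". The prior is uninformative. Table 2 lists the expected standard errors, 0.867 for 150 patients and 0.967 for 120.

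The closing sentence then says that "there is a high chance (>90%) of concluding a treatment benefit if the true difference between the groups is at least 1.5 h". The Table 2 caption uses similar language, calling the entries "expected posterior probabilities of concluding a positive treatment effect".

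**The concern.** The closing sentence conditions on the true difference only and speaks of reaching a conclusion. That describes an operating characteristic: how often, over repeated trials with a true effect of 1.5 h, the posterior probability would reach 0.80. The figures before it answer a different question, namely how sure one would be of a positive effect if the estimate happened to equal 1.5 h. In a real trial the estimate falls below the true value about half the time, and some of those estimates fail the rule.

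The rule decides whether a large international trial is recommended. A reader who takes the sentence at face value will put the risk of wrongly stopping at the design effect below 10%.

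**Working it through.** **Inputs.** Rule: posterior probability of at least 0.80 (Sample size; Analysis methods). Prior: uninformative (Sample size). Standard errors (SE): 0.867 for 150 patients and 0.967 for 120, which is 150 less 20% (Table 2). Design effect: 1.5 h, that is 14.8 − 13.3 (Sample size). Φ is the standard normal distribution function, and Φ⁻¹(0.80) = 0.8416.

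**Step 1: reproduce the article's figures.** With a flat prior and a normal likelihood, the posterior probability of a positive effect is Φ(estimate / SE).

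- 150 patients: Φ(1.5 / 0.867) = Φ(1.730) = 0.958; stated 0.958.
- 120 patients: Φ(1.5 / 0.967) = Φ(1.551) = 0.940; stated 0.939.

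All 18 posterior probabilities in Table 2 are reproduced to within 0.001 by this formula. The table is right for what it computes.

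**Step 2: confirm that the estimate was held fixed.** If the estimate varied around 1.5 h with SE 0.867, its central 90% range would be 1.5 ± 1.645 × 0.867, or 0.07 to 2.93 h. The posterior probability would then range from about Φ(0.085) = 0.53 to above 0.999. The printed interval is 0.946 to 0.97. With the estimate at 1.5 h, that corresponds to an SE between about 0.80 and 0.93. The printed spread thus fits variation in the estimated SE alone.

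**Step 3: probability of meeting the rule.** The rule is met when the estimate is at least 0.8416 × SE.

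- 150 patients: threshold 0.8416 × 0.867 = 0.73 h.
- 120 patients: threshold 0.8416 × 0.967 = 0.81 h.

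For a true difference d, the probability of meeting the rule is Φ(d / SE − 0.8416).

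| Patients analysed | SE | Article's posterior probability at 1.5 h | Probability of meeting the rule, true d = 1.5 h | False no-go risk |
|---|---|---|---|---|
| 150 | 0.867 | 0.958 | Φ(1.730 − 0.842) = 0.813 | 0.187 |
| 120 (20% loss) | 0.967 | 0.939 | Φ(1.551 − 0.842) = 0.761 | 0.239 |

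**Step 4: what >90% would take.** Since Φ⁻¹(0.90) = 1.2816, the true difference needed is (0.8416 + 1.2816) × SE. This is 2.1232 × 0.867 = 1.84 h with 150 patients and 2.1232 × 0.967 = 2.05 h with 120. Alternatively, at 1.5 h and 150 patients, the threshold would have to fall to Φ(1.730 − 1.2816) = 0.67. The value 0.958 itself is the probability of meeting a threshold of 0.50, that is, of any positive estimate.

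**Check on the approximation.** Step 3 treats the SE as known. Simulating 20,000 trials per sample size from the printed variance components, with the SE estimated in each trial, met the rule in 0.769 (150) and 0.720 (120) of trials. The same formula with the SEs those components imply (0.949 and 1.061) gives 0.770 and 0.717. Treating the SE as known therefore makes little difference. The levels are lower only because these SEs are larger than those in Table 2, a separate matter taken up in the objections.

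**The case against.** **The conditioning is disclosed.** The text states it beside the 0.958, the caption defines the effect as observed and true, and the column headings condition on the estimate. This stands as far as it goes: the headings are right and need no change. But the closing sentence drops the condition on the observed value, and the caption speaks of concluding.

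**Concluding benefit may not mean the 0.80 rule.** No other criterion is stated for the primary outcome. A stricter one widens the gap: a threshold of 0.90 gives 0.67.

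**At least 1.5 h includes larger effects.** It does, but the claim must also hold at 1.5 h, where it fails.

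**The design is unaffected.** This stands. Sample size, rule and model do not change, and about 81% may well be acceptable for a Phase 2 progression decision.

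A reader might also infer more than the article supports:

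- *That 150 patients has no justification other than the >90% figure.* The article also bases the number on what can realistically be recruited.
- *That the false no-go risk reaches 28%.* That uses SEs of 0.949 and 1.061, obtained from an unadjusted comparison with the printed variances: √[(32.90 + 10.97/13) × 4/150] = 0.949. The caption says its SEs come from the primary analysis models, which adjust for covariates. The gap from 0.867 is unexplained, not shown to be an error, and is not caused by the misreading.
- *That leaving out the 20% chance of a go under no effect is an error.* It follows directly from a 0.80 threshold with a flat prior, and a condensed article need not print it.

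**Conclusion.** The point holds for the closing sentence of the Sample size section and for the caption phrase. Under the stated rule, an uninformative prior and the SEs of Table 2, the probability of concluding benefit at a true difference of 1.5 h is about 81% with 150 patients and about 76% with 20% loss. The false no-go risk is about 19% to 24%, roughly twice or more what the sentence implies. More than 90% is reached only from a true difference of about 1.84 h, or 2.05 h with loss.

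The result assumes an approximately normal estimate and takes Table 2's SEs as correct. The posterior probabilities in Table 2 are sound as labelled by their column headings. The error lies in how they are summarised, and it does not show that the trial is too small for its purpose.

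**What to change.** Keep 150 patients and the 0.80 rule. Replace the closing sentence with one saying that, with 150 patients, the probability of reaching a posterior probability of at least 0.80 is about 81% if the true difference is 1.5 h, and about 76% if 20% of participants are lost.

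Ideally the sponsor confirms these values by rerunning its own simulation with the estimate free to vary around the true effect, counting how often the rule is met, and adds the result to Table 2 as a column. Remove the reference to concluding from the caption, so that it describes expected posterior probabilities of a positive effect. The existing column headings can stay.

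The cost is one sentence, a caption edit and a short simulation run. No patients are added and the analysis does not change; the stated figure becomes less favourable.

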#### Analysis methods

Prior to final analysis, a full Statistical Analysis Plan will define analysis populations, outcome measure derivations, procedures for imputing missing data (and/or conducting analysis in the presence of missing data), and specific analyses for each endpoint, including covariate adjustments, sensitivity analyses and any further exploratory analyses. The CI will approve the final version.

Primary analyses will be on an intention-to-treat (ITT) basis, in which all patients are included in analyses in the group to which they are assigned at randomisation, regardless of study completion or protocol adherence. Sensitivity analyses will consider a per-protocol (PP) analysis (for which a minimum degree of compliance will be agreed by the Trial Management Group) and an appropriate randomisation-respecting efficacy analysis (for example, Principal Stratification).

The primary outcome measure will be analysed and interpreted within the Bayesian framework, estimating and reporting the posterior probability of a positive effect. If this posterior probability is 0.8 or more, then this would indicate that moving to a definitive trial is recommended. The primary analysis will use proper but uninformative prior distributions for all parameters in the model. Sensitivity analysis will consider more informative priors, based on previous published data, as sensitivity analyses.^27,28^ The outcome measure itself will be the time in each individual 24-h period that the patient’s glucose spends in the range [3.9, 10.0 mmol/L], thus each patient will have multiple readings within the 76 to 91 day range. These will be analysed using a hierarchical longitudinal repeated measures model, comprising random intercepts for patients and centres, and random slopes for time, as well as fixed effects for intervention arm, insulin use, time, time-by- intervention interaction and day 0 time in range. We will initially assume a linear effect of time, but alternative patterns of change will be considered when data are available. The Bayesian posterior probability of positive intervention effect will be reported, when using prior distributions for main effects and covariances that are proper and non-informative. An additional analysis will account for possible moderating effect of baseline insulin use on the outcome measure, by including a fixed effect for the interaction between baseline insulin use and the intervention arm. Finally, for an ancillary analysis, we will obtain a single mean average time per day in normal range for each patient, and fit a conventional linear regression model, adjusting for fixed effects of insulin use, mean baseline glucose level and random intercept effects for randomising centre. This analysis will allow comparison between our results and other published trials using such analysis approaches.

Table 3 lists the planned analysis approach for the secondary and exploratory outcome measures. In general, analyses will take the form of regression models that adjust for the stratification factors, reported as estimated effect sizes with 95% confidence intervals. Analyses of “time per day” with glucose in a given range will be derived and analysed analogously to the primary outcome measure, though not within the Bayesian framework.

**Table 3. table3-1479164120957934:** Summary of planned statistical analysis approaches for the secondary and exploratory outcome measures.

Outcome measure	Brief analysis plan
Secondary	
Time per day in euglycaemia [3.9, 10.0 mmol/L] (at days 16–30)	Multi-level longitudinal mixed effects linear regression model, adjusted for random centre intercept effects*, fixed effects of insulin use, baseline glucose, time, time-by-treatment interaction and day 0 time in euglycaemia, random effects for patient and patient by time.
Time per day in hyperglycaemia (>10.0 mmol/L) (at days 76–91 and days 16–30)	
Time per day in hypoglycaemia <3.9 mmol/L) (at days 76–91 and days 16–30)	Ancillary analysis: linear regression model, adjusted for fixed/random centre effects*, fixed effects of insulin use and baseline glucose level.
HbA1c	Linear regression, adjusted for fixed / random centre effects*, fixed effects of insulin use and baseline value.
Weight	
Blood Pressure	
DTSQs scores	
EQ5D-5L utility score	
ADDQol scores	
(all at day 91)	
Exploratory	
Time per day in significant hypoglycaemia [<3.0 mmol/L) (at days 76–91 and days 16–30)	Multi-level linear regression model, adjusted for random centre effects*, fixed effects of insulin use, baseline glucose, time, time-by-treatment interaction, random effects for patient and patient by time.
Time per day in extreme hyperglycaemia [< 2.5 mmol/L) (at days 76–91 and days 16–30)	
	Ancillary analysis: linear regression model, adjusted for fixed / random centre effects*, fixed effects of insulin use and baseline glucose level.
Proportions of patients	For all except deaths: Poisson regression, including offset term for duration of follow-up, adjusted for fixed effects of insulin use and random centre effects. Unadjusted differences in proportions between groups.
+ experiencing severe hypoglycaemia that requires third party assistance (in months 1–3 and 4–12) + experiencing MACE within	
maximum 12 months	
hospitalised for diabetes-related causes within maximum 12 months	
+ deceased within maximum 12 months (all causes)	For deaths: Summary statistics by centre, insulin status and group. Unadjusted differences in proportions deceased in the two groups.
Time until first	Kaplan-Meier estimates of proportions event-free, stratified (by centre and insulin use), log-rank test. Time-to-event regression model (e.g. Cox proportional hazards, accelerated failure) adjusted for fixed effect of insulin use and random centre effects*.
+ MACE	

#### Economic evaluation methods

The Cost-Effectiveness analysis will be performed according to the reference case guidance for technology appraisals set out by NICE.^30^

At 91 days, a cost-consequences analysis will be performed in order to contrast the difference in health care cost with the difference in EQ-5D-5L scores (converted to Quality-Adjusted Life Years (QALYs)), diabetes treatment satisfaction levels (measured using DTSQs) and time spent in euglycaemia between the intervention and standard care and control groups.

## Trial governance and oversight

Ethical approval was obtained from the Yorkshire and Humber Leeds East REC on 28th June 2017. (REC reference 17/YH/0163) Approval from the Health Research Authority (HRA) was received on 4th July 2017. The most recent amendment to the protocol was approved in April 2019.

The sponsor for the trial is the University of Leeds. Given the low risk of the intervention, oversight of the study is provided by a single Trial Safety and Oversight committee (TSOC) combining the roles of a Data Monitoring and Ethics Committee and a Trial Steering Committee. The TSOC comprises an independent statistician, two independent clinicians and an independent patient representative. No formal interim analyses of safety or efficacy will be performed, hence there are no rules or guidelines for early trial termination.

After completion of final analysis, the final trial dataset will be property of the trial team and held at CTRU, University of Leeds. The trial team has agreed for a copy of the final clinical study report to be shared with funders (Abbott and NIHR) as part of the contractual agreement, in addition to access to manuscripts and abstracts for publication or dissemination.

No release of trial data will take place until after publication of the main trial results. Access to the trial dataset for bona fide research purposes will require a signed legally-binding contract to ensure the data security and confidentiality of participants and defining particularly the data items requested and planned analyses. Participants will only be included in shared datasets if they consented. Data will be anonymised prior to any data transfer.

## Discussion

We describe the scientific rationale and design of the LIBERATES trial. This trial will recruit T2D patients with recent MI to test whether the use of Freestyle Libre leads to better glycaemic control compared with standard care consisting of self-monitoring of capillary glucose measurements. This trial aims to establish differences in glucose parameters between two study groups in a relatively limited number of patients, akin to other CGM studies. Data from the work will establish the feasibility of a larger scale study investigating hard clinical outcomes in individuals with T2D and recent MI, including MACE and mortality.

Glycated haemoglobin is a convenient outcome measure of average plasma glucose levels over a 3-month period. However, it does not provide an assessment of hypoglycaemia, nor variability in glucose levels, both of which are associated with adverse outcomes. CGM permits such swings to be detected, providing a more comprehensive assessment of glycaemia.

Previous randomised controlled trials with Freestyle Libre in T2D are limited to two studies. The REPLACE study (NCT02082184^22^) recruited 224 inadequately controlled, insulin-treated T2D patients, having HbA1c between 7.5% and 12% (58–108 mmol/mol). Individuals were randomised on 2:1 basis to intervention using flash glucose monitoring and standard control group employing SMBG for glucose measurements. Flash glucose monitoring did not show improvement in HbA1c, although a pre-specified subgroup analysis of patients younger than 65 years showed significant reduction in HbA1c by 5 mmol/mol in the Libre group compared with standard care (after adjustment for baseline). A more recent study on 101 insulin-treated individuals with T2D has shown a significant reduction in HbA1c and improvement in quality of life measures in the group managed with Freestyle Libre compared with SMBG.^24^

The LIBERATES trial is novel in that it targets a higher vascular risk population with T2D patients. This is a particularly difficult group due to patient concerns following a life-threatening event, the need to undergo various procedures and start of new therapies. Therefore, glycaemia often becomes of secondary importance despite the documented association between high glucose levels and adverse clinical outcome.

The planned analysis of LIBERATES is also novel in that continuous glucose traces will not be averaged to create a single value per patient: rather, the trace will be partitioned into individual daily readings, to be analysed as a repeated measures longitudinal analysis. By doing so, the information in the data can be maximised with changes in glucose control modelled over time, and the correlation between measurements made on the same patient taken into account. However, traditional analysis of the aggregated data will also be undertaken to enable comparison with published results from RCTs and observational studies.

The LIBERATES trial will provide valuable information on the use of Freestyle Libre in T2D patients with recent MI who are at risk of hypoglycaemia. It will clarify the role of Freestyle Libre in improving glycaemic parameters and quality of life in this highly stressed group. In particular, multiple glycaemic markers will be studied, thus providing a comprehensive assessment of glycaemia to aid the clinical management of these patients. Also, it will provide preliminary data for a large multinational clinical outcome study investigating the use of this device to improve short and medium-term clinical outcome in diabetes patients post MI.

